### Sample size calculations

To account for cluster randomisation, sample size calculations are based on recent sample size requirements developed by Heo and Leon [35] to detect intervention by time interactions in longitudinal cluster randomized clinical trials. To detect differences between groups, five schools (with an average of 75 students each) will need to be randomly allocated to receive the *Climate Schools* intervention, and five schools to a control group. Based on a recent school-based trial conducted by the investigators [33], in which there was an average of 125 students per grade in Sydney secondary schools, recruiting 75 students per school appears feasible. This will achieve 80 per cent power to detect a standardized between-group mean difference of 0.20 (p = 0.05) in outcomes at the end of the trial with three measurement occasions. An effect size of 0.20 for use is comparable to previous trials of universal drug prevention programs [19,27]. To account for school dropouts during the trial, which we expect to be approximately 10 per cent [28], we aim to recruit at least 12 schools, providing a minimum of 900 students at baseline to test the effect of the intervention in the overall group.

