### Assessment

Students in both groups will complete an online self-report questionnaire at baseline, immediately post-intervention and 6-, 12- and 24-months later. Students will be required to create a unique username and password to register with the study website and will use these details to login to complete each survey. Upon registration participants will be automatically assigned a unique code, which will be used to link student data across the survey time points whilst maintaining confidentiality. Table 2 outlines the assessment and intervention timeline for both groups.

**Table 2 T2:** Assessment and intervention timeline

	**Baseline**	**Climate Schools program**	**Immediate Post-test**	**6 month F/U**	**12 month F/U**	**24 month F/U**

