### Statistical analysis

Single-level analyses; one-way analyses of variance (for normally distributed data), Chi-square (for binominal data), and Mann–Whitney U-test (for non-normally distributed data) will be used to examine baseline equivalence and attrition between groups. Due to the multi-level and hierarchical nature of the data, mixed effects regression will be used to examine intervention by time interaction effects. To account for intracluster variance within schools, intervention effects will primarily be examined using hierarchical linear modelling (HLM) for normally distributed data and hierarchical generalized linear modelling using a Poisson distribution for count data. Outcome variables will be centred at post-test to allow for comparisons between groups immediately after the intervention, and growth terms will be analysed to determine the magnitude of the follow-up effects. Analyses will be conducted using the program Stata. If unconditional models reveal that less than 10% of systematic variance exists between school level for any outcome variable, HLM will be abandoned and single-level analyses will be used [4]. For these variables, ANCOVAs utilising the SPSS GLM procedure will be conducted to account for any baseline differences that might exist between groups. For multiple comparisons Bonferroni adjustments will be made. Effect sizes, odds ratios and 95% confidence intervals will also be calculated.

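### For outcomes kept in the mixed model, the plan takes the size of follow-up effects from growth terms, which measure how the post-test difference changes and not the difference at 6, 12 or 24 months

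*Protocol article*

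**What the plan says.** The Statistical analysis section states that "mixed effects regression will be used to examine intervention by time interaction effects". It then gives two readings from the model. The first is the early comparison: "Outcome variables will be centred at post-test to allow for comparisons between groups immediately after the intervention". The second concerns the later surveys: "growth terms will be analysed to determine the magnitude of the follow-up effects". The section adds that effect sizes, odds ratios and 95% confidence intervals will be calculated, without saying for which contrast or at which visit. Outcomes with less than 10% of their variance between schools leave the hierarchical model for ANCOVA.

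The Assessment section sets five occasions: "Students in both groups will complete an online self-report questionnaire at baseline, immediately post-intervention and 6-, 12- and 24-months later". Table 2 places baseline, programme and post-test all in Term 1 of 2014.

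The Sample size calculations section describes its method as one "to detect intervention by time interactions in longitudinal cluster randomized clinical trials", and states the target as a "standardized between-group mean difference of 0.20 (p = 0.05) in outcomes at the end of the trial".

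**The concern.** The sentence does more than leave detail to a later document. It names the quantity that is to give the size of the follow-up effects. With time zero at post-test, that quantity is a rate of change in the effect, whereas the sample size section frames its target as a level at the last visit.

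The two agree only when the arms are equal at time zero and separate afterwards. Time zero here falls after all four lessons, when knowledge and intentions, both primary outcomes, would be expected to have moved already. For those outcomes the likely patterns are hold or fade. A plan that reads the follow-up effect from the slope would show nothing for a benefit that holds, and a term of the opposite sign for one that fades but is still present at 24 months. Whether benefit lasts is what the later surveys are there to show.

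**Working it through.** **1. The plan's own figure.** The trial is sized at five schools of 75 students per arm, for 80% power to detect 0.20 SD at the end of three occasions. I used a slope-difference test under a random-intercept model with occasions 0, 1, 2 (sum of squares 2), slope 0.20/2 = 0.10 per occasion and two-sided 5%:

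schools per arm = 2(1 − r)(1.960 + 0.842)² / (75 × 2 × 0.10²)

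The within-student correlation r is not stated. r = 0.50 gives 5.23, r = 0.55 gives 4.71 and r = 0.60 gives 4.19. Five schools is therefore reachable for plausible r, though not from the stated inputs alone. The sample size is not in dispute. What matters is the step from 0.20 at the end to 0.10 per occasion: it treats the slope as the end-of-trial difference, which is valid only if the arms are equal at time zero. That can hold at baseline. It does not hold at post-test if the programme has had an immediate effect.

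**2. The algebra.** Let t be time since post-test, a the arm term and b the arm-by-time term.
- Effect at post-test: a.
- Effect at time t: a + b·t. In a Poisson model the rate ratio is exp(a + b·t).
- The growth term b equals (effect at t − effect at post-test) / t.

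**3. Growth from post-test onwards.** I assume post-test is 1 month after baseline and later surveys are timed from baseline, as in the Abstract, so t = 0, 5, 11, 23 months. Benefit is coded positive and changes linearly.
- Held at 0.20 SD: b = 0; effect at 24 months 0.20 SD.
- 0.40 fading to 0.20 SD: b = −0.20/23 = −0.0087 SD per month; effect at 24 months +0.20 SD.
- 0.30 fading to 0.10 SD: b = −0.0087 SD per month; effect at 24 months +0.10 SD.
- 0 building to 0.20 SD: b = +0.0087 SD per month; effect at 24 months 0.20 SD. Here b × 23 recovers the effect.

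The same 24-month effect of 0.20 SD thus gives a growth term that is zero, negative or positive, depending only on the path.

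**4. Baseline included in one straight line over five occasions.** With post-test at 1.5 months, t = −1.5, 0, 4.5, 10.5, 22.5 (mean 7.2, sum of squares 379.8) and the arms equal at baseline:
- Held at 0.20: cross-product 1.74, slope 1.74/379.8 = 0.00458 per month, or 0.11 SD over 24 months (0.107 to 0.113 for post-test at 1 to 2 months).
- 0.30 fading to 0.10: −0.04 SD over 24 months.
- 0.40 fading to 0.20: about +0.01 SD over 24 months.

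The growth term misstates these three benefits under this coding too, but the exact zero for a sustained effect disappears.

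**5. How often a fading benefit would show a significant negative slope (illustration only).** With t = 0, 5, 11, 23 the mean is 9.75 and the sum of squares 294.75. With 450 students per arm and r = 0.5, the standard error is √(2 × 0.5 / (294.75 × 450)) = 0.00275.
- 0.40 to 0.20 SD: z = −3.17, 89% (82% to 94% for r = 0.4 to 0.6).
- Same case, t distribution on 10 degrees of freedom for 12 schools: 81%.
- Adding a school-level SD of 0.10 in the 23-month change: 56%, or 47% with five schools of 75 per arm (8 degrees of freedom).
- 0.20 to 0.10 SD, on the assumptions of the first line: z = −1.58, 35%.

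These rates move widely with assumptions the protocol does not fix. The zero and the sign in step 3 depend on none of them.

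**The case against.** The strongest reply is that the sentence names two quantities, the post-test comparison and the growth terms, and that together they determine the effect at every follow-up. A negative slope would then appear beside a positive post-test difference, and which contrasts are tabulated is detail an article may leave out. Part of this stands: nothing says the post-test difference is discarded, so a reader who infers that the trial would report the programme as harmful or without lasting benefit goes further than the document does. But the plan does not say the two terms will be combined. A confidence interval for the sum also needs their covariance, and the sentence assigns the magnitude of follow-up effects to the growth terms.

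Four limits stand in full:
- Time coding is not stated, so the exact zero holds only if growth runs from post-test.
- Use is also a primary outcome. Since post-test falls in the same school term as the programme, lifetime or six-month use should differ little there, and an effect that builds later is the case the growth term measures well. The sample size section ties its 0.20 to use and speaks of interactions over time, so its conflict with the analysis section is partial.
- Outcomes sent to ANCOVA have no growth term.
- Starting effects of 0.30 or 0.40 SD are assumptions; the protocol's only figure is 0.20. A reader might take the 89% in step 5 as the trial's risk of an adverse-looking result. The protocol supports no such figure.

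**Conclusion.** The point holds for outcomes kept in the mixed model. The growth term is the wrong quantity for the size of a follow-up effect, and it differs from the end-of-trial mean difference the sample size section names. With growth coded from post-test, a sustained benefit scores 0 and a fading but positive one takes the opposite sign. With baseline in a single linear slope, a sustained 0.20 SD scores about 0.11 SD over 24 months. Both results assume linear change and, for the second, arms equal at baseline and post-test 1 to 2 months later. Knowledge and intentions are most exposed. This should be corrected before analysis because the wording fixes the wrong estimand, but it does not invalidate the design, the model or the sample size.

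**What to change.** Replace the clause on growth terms with: *Follow-up effects will be estimated as model-based between-group contrasts with 95% confidence intervals at 6, 12 and 24 months from the same mixed model (arm term plus arm-by-time terms at that occasion, or time as a categorical factor); growth-term interactions will be reported only as describing persistence or decay of the effect.*

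In the same sentence, say that time, not the outcome, is centred at post-test. This is a wording correction: a centred count could be negative or non-integer and could not enter the stated Poisson model. State also whether baseline is part of the growth trajectory.

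The cost is one sentence and a post-estimation command (lincom or margins) in Stata, which the plan already names. No extra data, schools or students are needed.

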### Study design

A cluster RCT will be conducted in 12 secondary schools in the greater Sydney region between 2014 and 2016. Six schools will be randomly assigned to the C*limate Schools* intervention group, and six schools to the control group. Cluster randomisation will be employed in this study to avoid contamination of the control group by the intervention group through student communication [34]. To evaluate the *Climate Schools* intervention for efficacy, students in both groups will complete five online self-report questionnaires over the three year study period. The trial has been approved by the University of New South Wales Human Research Ethics Committee (HREC HC13075).

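### The rule that drops the school level when under 10% of variance lies between schools leaves those outcomes tested as if students, not schools, had been randomised

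*Protocol article*

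**What the plan says.** Under Study design, whole schools are the unit of randomisation: "Six schools will be randomly assigned to the" intervention arm and six go to control. Sample size calculations sets the cluster size: "five schools (with an average of 75 students each) will need to be randomly allocated to receive the" programme, with five more as controls. Recruitment is raised to 12 schools and 900 students to allow for about 10% of schools dropping out.

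Statistical analysis first chooses mixed-effects models because the data are hierarchical. It then makes that choice conditional. If unconditional models show that "less than 10% of systematic variance exists between school level for any outcome variable, HLM will be abandoned and single-level analyses will be used", the replacement is stated: "ANCOVAs utilising the SPSS GLM procedure will be conducted to account for any baseline differences that might exist between groups". No school term, cluster-robust standard error or school-level test is given for that branch. The section also promises: "For multiple comparisons Bonferroni adjustments will be made".

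The article gives no ICC for any outcome and does not define what it counts as systematic variance.

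**The concern.** The damage done by ignoring clusters depends on the ICC and the cluster size together, so a fixed cut-off on the between-school share cannot show that clustering is negligible. With 75 students per school, 10% is far too lenient. Below it, the plan treats about 450 students per arm as independent when only six schools per arm were randomised.

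The rule applies to any outcome, so it can govern the primary ones: knowledge, intentions and use. Where it applies, standard errors are too small, confidence intervals too narrow and p-values too low. A programme with no effect could then be reported as effective.

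**Working it through.** **Inputs from the article.** Six schools per arm (Study design); 75 students per school, 5% significance level, standardised difference 0.20 and 80% power (Sample size calculations); 10% cut-off (Statistical analysis).

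**Assumptions.** Two-sided test; ICC from 0.01 to just under 0.10; all 75 students per school analysed; the 10% read as a share of total variance.

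**The plan's own figure.** The article says: "This will achieve 80 per cent power to detect a standardized between-group mean difference of 0.20". With 5 × 75 = 375 students per arm and no design effect, power is Φ(0.20 × √(375/2) − 1.96) = Φ(0.779) = 78.2%, within two points of 80%. The slope-difference formula for three equally spaced occasions also gives 78.2%, at an assumed within-student correlation of 0.5. The stated power is therefore roughly reproduced, but it does not reveal an ICC.

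**Error of the single-level test.** The design effect is DE = 1 + (75 − 1) × ICC. A nominal 5% test that ignores school has actual error 2[1 − Φ(1.96/√DE)].

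| ICC | DE | Type I error |
|---|---|---|
| 0.01 | 1.74 | 13.7% |
| 0.02 | 2.48 | 21.3% |
| 0.05 | 4.70 | 36.6% |
| 0.099 | 8.33 | 49.7% |

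With 50 analysed students per school, the error is 10.8% at ICC 0.01 and 29.1% at 0.05.

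**The whole rule, simulated.** 20,000 trials per setting, 6 v 6 schools of 75, no true effect. The ICC was estimated by analysis of variance. A single-level test was used below 10%, and a school-level t-test with 10 degrees of freedom otherwise.

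| True ICC | Sent to single-level test | Error of the whole rule | Error if school is always kept |
|---|---|---|---|
| 0.01 | 100% | 14% | about 5% |
| 0.02 | 100% | 21% | about 5% |
| 0.05 | 96% | 35% | about 5% |
| 0.08 | 75% | 33% | about 5% |
| 0.10 | 56% | 27% | about 5% |

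At a true ICC of 0.10, the trials that dropped the school level had an error of 44%. An ICC estimated from 12 schools is too imprecise to choose the analysis.

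**Baseline adjustment.** The fallback is an ANCOVA, so it was also simulated with a baseline covariate (3,000 trials per setting; correlation of school effects over time 0.5 to 0.95, within-student correlation 0.5 or 0.7). Error was about 8% to 19% at ICC 0.01, 18% to 44% at 0.05 and 27% to 57% at 0.099. Adjustment helps when school effects are very stable over time and can hurt when they are not. It does not restore 5% in any of these settings.

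**Bonferroni.** Suppose the 5% is divided by three (an assumption, since the article does not fix the number of comparisons). The nominal level is 1.67% and the critical value 2.394. The error per test is 2[1 − Φ(2.394/√DE)]: about 7% at ICC 0.01, 13% at 0.02 and 27% at 0.05. The rates fall, but each stays well above 1.67%.

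**The case against.** The best defence is that every error rate above rests on an assumed ICC. That is right. A reader might infer that nearly every outcome would go to single-level tests, or that one range of false-positive rates describes the trial. The document supports neither. Diversion is almost complete at ICCs up to about 0.05, but only a little over half at 0.10. For very small ICCs the inflation is modest: about 9% at 0.005.

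The wording about systematic variance could also exclude occasion-level residual variation. The cut-off would then be a smaller share of total variance, and the figure of about 50% just below it would be too high. The inflation at ICC 0.01 to 0.05 would still apply to any outcome that the rule diverts.

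Further readings are tempting but are not established:

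- **ANCOVA for yes/no and count outcomes.** The rule covers any outcome variable, but the section ties HLM to normally distributed data, names a separate Poisson model for counts and promises odds ratios. This is an ambiguity.
- **Loss of students with a missing follow-up.** The article does not describe missing-data handling, which is commonly left to the analysis plan.
- **Normal-theory z tests in the hierarchical models.** The article does not say that they will be used.
- **Single-level tests of baseline equivalence and attrition.** These are stated: single-level methods "will be used to examine baseline equivalence and attrition between groups". They are descriptive checks, do not decide efficacy and do not carry this point.

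The core is untouched. The rule is explicit, and nothing in the document corrects the branch it opens.

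**Conclusion.** The concern holds in conditional form, and the rule should be changed before analysis. As written, any outcome with an estimated between-school share under 10% is tested without regard to the unit of randomisation. With 75 analysed students per school, a nominal 5% unadjusted single-level test has about 14% to 37% error for assumed ICCs of 0.01 to 0.05. The baseline-adjusted version gave about 8% to 44% over the same ICCs. Just under the cut-off the unadjusted figure is about 50%, if the 10% is a share of total variance. Fewer analysed students per school would lower these figures. The share of outcomes affected cannot be stated, because no ICC is given.

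**What to change.** Delete the 10% rule and the single-level ANCOVA fallback. Keep the school effect in the between-arm analysis of every outcome, whatever the estimated ICC, using a hierarchical model suited to the outcome type. Base inference on 12 schools: either small-sample degrees of freedom, such as Kenward–Roger, or a school-level analysis with 12 − 2 = 10 degrees of freedom. Baseline values can still enter these models as covariates.

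A secondary change: if attrition is compared between arms, account for school there too, because the plan expects whole schools to drop out.

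The cost is a change of wording with no new data. Confidence intervals will be wider and correctly sized, so some effects that a single-level test would call significant will not be.

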## Discussion

The aim of the current study is to implement and evaluate the *Climate Schools: Ecstasy and Emerging Drugs Module* through a cluster RCT among Australian students*.* It is hypothesised that the *Climate Schools* intervention will increase ecstasy and NED-related knowledge, reduce intentions to use ecstasy and NEDs in the future and prevent the uptake and reduce the use of ecstasy and NEDs. Given the considerable attention NEDs have received by policymakers, researchers and the media recently, a clear strength of the proposed study is that it is a timely intervention. The evaluation of the *Climate Schools: Ecstasy and Emerging Drugs Module* addresses the calls to action raised by major international bodies, such as the United Nations, to develop and implement universal prevention programs for NEDs among young people [9]. To our knowledge, this will be the first trial of an online, school-based prevention program designed to specifically target ecstasy and NED use among adolescents.

It is anticipated that the *Climate Schools: Ecstasy and Emerging Drugs Module* will build on the success of the existing *Climate Schools* courses [28-31], and provide schools with an interactive, affordable and evidence-based prevention program for ecstasy and NEDs that can be readily implemented by teachers. A further strength of the proposed study is the simultaneous delivery of education for ecstasy and NEDs. Due to the overlap between the substances, that is, NEDs are often manufactured to produce ecstasy-like psychoactive effects, they are both often available in pill form, and the age of use for both substances are similar, it is logical to integrate prevention for ecstasy and NEDs. By delivering one four-lesson program for both ecstasy and NEDs, teachers are able to educate students about these drugs in a time-effective manner, whilst maximising prevention messages. Furthermore, through its online delivery, the *Climate Schools* intervention is likely to be appealing to teenagers and foster interactive learning and high student engagement. Of most significance, if the *Climate Schools: Ecstasy and Emerging Drugs Module* can prevent the uptake and reduce the use of ecstasy and NEDs, it is possible that the program can minimise the potential burden of disease, social costs, and disability associated with their misuse.
